## **Executive Summary**

### **Introduction**

Maternal mortality, low birth weight, and early infant mortality remain important public health problems in most developing countries. Although it is widely acknowledged that poor prenatal nutritional status in developing countries adversely affects maternal and infant health, prenatal nutrient supplementation is generally limited to the provision of iron/folate tablets. This contrasts sharply to the prevailing situation in developed countries, where long-standing policies of routine antenatal care include multi-vitamin/mineral supplements.

The potential importance of prenatal multinutrient supplements is demonstrated by several studies in developing countries which documented substantial improvements in maternal and infant health following supplementation with individual nutrients or combinations of nutrients including vitamin A, iron, zinc, and folate. Indeed, one recent report from Nepal found that routine supplementation of women with vitamin A (retinol) or  $\beta$ -carotene, alone, reduced pregnancy-related mortality by 40%. Prenatal multinutrient supplementation is, therefore, strongly indicated and further underscored by the high overall prevalence of micronutrient deficiencies in developing countries.

The encouraging effects of prenatal nutrient supplementation on maternal and infant health have generally been obtained under somewhat artificial highly supervised trial conditions. Before clear policy decisions can be made regarding the provision of prenatal multi-micronutrient supplements, it is also necessary to determine the health benefits of multinutrients when delivered through existing programs of prenatal care.

### **Specific Aims**

Helen Keller International (HKI)-Indonesia, therefore, proposes to conduct a **Supplementation with Multiple Micronutrients Intervention (SUMMIT)** to determine the health impact of pre-natal multiple micronutrient distribution through the existing health infrastructure. The primary purpose of the intervention is to determine if daily prenatal multi-micronutrient supplementation will:

1. Reduce the frequency of maternal mortality
2. Reduce the proportion of low birth weight neonates
3. Reduce neonatal and infant mortality rates

### **Intervention area and population**

The proposed intervention site is the tropical island of Lombok, NTB, which remains one of the poorest regions of the country with correspondingly poor health indicators. Infant and under-five mortality per 1000 live births are 110 and 149, respectively, with an estimated maternal mortality ratio ranging from 400 to 800 per 100,000 live births. The island occupies approximately 4,739 km^2 and is home to 2.6 million people. At 568 persons/km^2 it is one of the most densely populated regions in Indonesia.

Reduction of maternal and infant mortality are priorities of the Ministry of Health (MOH) of Indonesia. In the last decade several maternal health promotion activities have been implemented through the MOH, including placement of trained midwives in the majority of villages, and education programs to improve maternal health before and during pregnancy. Thus, the Indonesian health structure on Lombok is well positioned to assess the programmatic impact of prenatal multinutrient supplementation on maternal mortality, low birth weight, and infant health.

## **SUMMIT activity design and methodology**

*Outcomes:* The SUMMIT activity is a controlled trial designed to assess the relative impact of a prenatal multi-micronutrient tablet in comparison to the current MOH iron/folate tablet on frequency of maternal mortality as assessed by both the maternal mortality ratio (MMR), defined as maternal deaths per 100,000 live births, and the maternal mortality rate (MMRT), defined as the death of a woman while pregnant or within 42 days of termination of pregnancy from any cause aggravated or related to the pregnancy, expressed per 100,000 pregnancies. Two additional main outcomes of the SUMMIT activity are proportion of low birth weight infants, and infant mortality, including neonatal mortality. Secondary outcomes to be assessed include maternal morbidity, neonatal development, and nutritional status during pregnancy and lactation. In addition to examining the effect of multi-nutrients, we will document the effect of education and social marketing of the SUMMIT activity by comparing outcome rates in the iron/folate arm of the intervention area to corresponding rates in designated villages where standard prenatal care practice will continue. In a 20% subsample of pregnancies biochemical status for micronutrients, including, iron, zinc, and vitamin A, will be determined.

*Sample Size:* The SUMMIT activity will aim to detect a reduction in both MMR and MMRT of at least 30% with a power of 80% and significance level of 0.05. Current estimates of the MMR in various districts on Lombok range from 400 to 800 maternal deaths per 100,000 live births and randomization for the trial will be by clusters consisting of geographic areas serviced by each of the 300 midwives providing prenatal care. Assuming 400 maternal deaths per 100,000 live births and a 10% loss to follow-up, the trial would require enrollment of 102,000 live birth pregnancies allocated to either an iron/folate or multinutrient supplement to detect a 30% reduction in MMR. Because not all pregnancies result in a live birth, it is estimated that the required sample size be increased an additional 15% to 120,000. This sample size will also allow detection of similar reductions in MMRT. It is proposed that enrollment be phased in over a 6-month period and continue for at least 2 years to accommodate seasonal effects. The phased in implementation along with the approximately 72,000 pregnancies occurring each year throughout the trial area yields a projected enrollment of 126,000 pregnancies. The additional margin of enrollment provides the ability to detect reductions in MMR as little as 22% if ratios approach 800 per 100,000 live births. With regard to low birth weight and infant mortality rates, the projected sample size will allow detection of at least a 10% reduction in low birth weight and infant mortality rates, including neonatal mortality rates. Equally important is determination of the impact of the social marketing and education programs that will accompany the trial implementation in the intervention area. Data concerning outcome variables in the absence of the intervention will be collected during the phase-in period prior to enrollment. This will result in the ability to detect at least a 25% difference in MMR between the iron/folate arm of the intervention area compared non-intervention areas.

*Supplementation:* Pregnant women will be provided with either an iron and folate tablet or another multi-micronutrient tablet containing iron, folate, vitamins A, B1, B2, B6, B12, C, D, and E, along with niacin, zinc, copper, selenium, and iodine. Supplements will be provided by existing MOH midwives, and be distributed from the first antenatal consultation for a confirmed pregnancy until three months postpartum. The midwives will distribute the supplements monthly as 30-tablet sachets, as is current MOH practice, and monitor the health impact through routine prenatal care visits and compliance checks. Additional compliance monitoring will be conducted by HKI field workers through spot-checking of pill counts and biochemical indices.

*Monitoring:* In addition to the distribution of supplements, midwives will continue to record the results of routine prenatal examinations, attend deliveries and record data on labor and delivery, birth weight, and APGAR scores of neonates. All of these activities are currently part of the normal maternal care protocol implemented by the MOH. The implementation of these activities will be strengthened in all villages by training and community promotion. HKI field workers will collect additional data at enrollment, at 36 weeks of gestation, and at 12 weeks postpartum on socio-economic status, food intake, and anthropometry. Deaths will be detected through the longitudinal surveillance of participants and also through the quarterly island-wide demographic surveillance system. The dual surveillance will allow the trial to document all maternal deaths (up to and exceeding 12 weeks postpartum), to allow evaluation of MMR and MMRT, and all infant deaths occurring beyond the 12-week visit. Lastly, it will allow monitoring of mortality in the non-intervention villages. For all maternal and infant deaths verbal post-mortem assessments will be made to determine the associated causes and conditions.

*Implementation schedule:* The trial will be carried out over five years in 3 distinct stages broadly scheduled as follows; Phase I- Preparation and training from December 1999-August 2000, Phase II-Supplementation and follow-up from September 2000-September 2003, and Phase III-Analysis and report preparation from October 2003-October 2004.

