Current practice in Indonesia is for pregnant women to receive at least 90 tablets containing 60 mg iron and 250  $\mu$ g folate to be taken on a daily basis as part of routine antenatal care. For the SUMMIT activity distribution of tablets will be more frequent with participants receiving tablets daily from the first antenatal clinic attendance to 90 days post-partum. The supplements will be either the multi-micronutrient combination or a matching tablet containing 30 mg iron and 400  $\mu$ g folate. This strategy and formulation are proposed to maximize health benefit and compliance, and minimize any side effects. Thus, the intervention will compare the impact of a multi-micronutrient supplement for pregnant women to that of an iron/folate supplement.

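### The control is not the current MOH tablet, so the iron/folate arm versus non-intervention contrast reflects a whole programme package and cannot isolate education, social marketing or midwife attendance

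*Protocol*

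**What the plan says.** **Comparator.** The Executive Summary (Outcomes) gives the randomised comparison as a "multi-micronutrient tablet in comparison to the current MOH iron/folate tablet". Section IV describes the current tablet differently: "Current practice in Indonesia is for pregnant women to receive at least 90 tablets containing 60 mg iron", with 250 µg folate. It then gives the trial control as a matching tablet of 30 mg iron and 400 µg folate, on a changed schedule: "For the SUMMIT activity distribution of tablets will be more frequent with participants receiving tablets daily from the first antenatal clinic attendance", continuing to 90 days postpartum. Section VIII.B.2 repeats the control dose and states that refusers and women in pre-intervention areas stay on the standard government tablet.

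**Programme contrast.** The Outcomes paragraph says "we will document the effect of education and social marketing of the SUMMIT activity by comparing outcome rates in the iron/folate arm" with rates in "designated villages where standard prenatal care practice will continue". The Sample Size paragraph of the summary adds: "Equally important is determination of the impact of the social marketing and education programs that will accompany the trial implementation". Section VIII.B.3 sizes the contrast at 54,000 non-intervention against 63,000 iron/folate pregnancies, with a detectable effect of 20-25%. Section VIII.B.8 reads the baseline version of the contrast as the mortality effect of more births attended by midwives. Section VIII.B.12 says the components can be assessed one by one. Sections V and VIII.B.12 carry the results into cost-benefit analysis.

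**The concern.** The comparator label and the programme contrast are linked. If the control really were the current tablet, the iron/folate arm would differ from standard-care villages only in what accompanies the tablets. Because it is not, moving from standard care into the iron/folate arm changes the formulation and the planned course as well. The same contrast is also credited to two different causes: education and social marketing in the summary, midwife attendance in VIII.B.8. It cannot isolate both.

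The summary ranks this question equally with the supplement question, and section V says the answer will inform government budget decisions. Followed as written, the plan would credit promotion or midwife attendance with whatever the changed tablet and the passage of time contribute, or would let those hide a real promotion effect. The label has its own cost: a reader of the summary would take the randomised result as multi-micronutrients against current policy, when it is multi-micronutrients against a 30 mg/400 µg tablet.

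**Working it through.** **1. Tablets (sections IV and VIII.B.2).** Iron per tablet: 30/60 = 0.5. Folate per tablet: 400/250 = 1.6. The label in the Outcomes paragraph is therefore wrong.

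**2. What differs between the two sides of the programme contrast.**

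| Factor | Non-intervention or baseline | Iron/folate arm | Source |
|---|---|---|---|
| Tablet | 60 mg iron/250 µg folate | 30 mg iron/400 µg folate | IV, VIII.B.2 |
| Planned course | at least 90 tablets | daily, first visit to 90 days postpartum | IV |
| Promotion | before phase-in | after phase-in | V |
| Midwife attendance | existing level | encouraged | VIII.B.8 |
| Calendar time | largely earlier (step 3) | largely later | VIII.B.2, VIII.B.3 |

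Section VIII.B.6 randomises the supplement code to midwives. The protocol does not state that phase-in order or non-intervention status is randomised. Longer supply that results from earlier first visits belongs to the promotion effect; only the scheduled extension is a separate change. The Monitoring paragraph ("The implementation of these activities will be strengthened in all villages by training and community promotion") leaves unclear whether midwife strengthening differs by area at all.

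**3. Calendar time.** Inputs: 72,000 pregnancies a year (VIII.B.1), so 18,000 per three months; a six-month baseline and start by thirds of villages at three-month steps (VIII.B.2); and, in the summary, "It is proposed that enrollment be phased in over a 6-month period". Thirds therefore start at months 0, 3 and 6.

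- Baseline: 72,000 × 0.5 = 36,000.
- Still waiting: months 0-3, 2/3 × 18,000 = 12,000; months 3-6, 1/3 × 18,000 = 6,000; together 18,000.
- Non-intervention total: 36,000 + 18,000 = 54,000, the figure in VIII.B.3.
- Enrolled: 1/3 × 18,000 + 2/3 × 18,000 + 1.5 × 72,000 = 6,000 + 12,000 + 108,000 = 126,000, the planned enrolment. Half is 63,000, the iron/folate figure.

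Starts at months 3, 6 and 9 would give 36,000 + 18,000 + 12,000 + 6,000 = 72,000 comparison pregnancies, which does not match. On the reading that fits, 36,000/54,000 = 67% of the comparison group precedes any supplementation. Of the iron/folate arm, 18,000/2 = 9,000, or 9,000/63,000 = 14%, falls within the phase-in.

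**4. The stated detectable effect uses these groups.** Normal approximation for two proportions, two-sided 0.05, pooled standard error under the null (SE0) and unpooled under the alternative (SE1): z = (|p1 − p2| − 1.96 × SE0)/SE1. At an MMR of 400 per 100,000 and a 24.3% reduction, p1 = 0.004000 and p2 = 0.003028. With 54,000 and 63,000, SE0 = 0.000345 and SE1 = 0.000349, so z = (0.000972 − 0.000676)/0.000349 = 0.85 and power is 80%. At an MMR of 600 the detectable reduction is 20.0%. The stated 20-25% thus reproduces from the full 54,000 against 63,000, without allowances for clustering, loss or non-live births.

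**5. Could analysis separate the factors?** No scheduled group receives promotion with the government tablet, or the trial control tablet without promotion. Refusers in intervention villages are self-selected and do not serve. No model can therefore separate tablet change from promotion. Calendar time could be adjusted for, but that relies on concurrent pregnancies. If the only ones were the inferred 18,000 waiting and 9,000 iron/folate, the detectable MMR reduction would be about 50%, 42% and 37% at MMR 400, 600 and 800 by the same method.

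**The case against.** The strongest reply is that the operative text is better than the summary. Sections IV and VIII.B.2 give both doses or the control dose openly, and section IV gives reasons for the change. Section VIII.B.3, which sizes the contrast, speaks of programme implementation apart from the multi-micronutrient effect, which is already close to a package reading. Section V can be read as a two-part split between accompanying activities and the supplement. The before/after element is disclosed, and handling of time trends is commonly left to the SAP. All of this stands. It confines the fault to the summary, VIII.B.8 and the component claim of VIII.B.12, with a clarification needed in section V. It does not remove the fault: the tablet change is tied to promotion by design, so an SAP cannot separate them, and these places state a causal meaning the contrast does not have.

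Four stronger readings are tempting and not supported.

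- *The trial hides its control dose or the randomised comparison is compromised.* The doses are stated, and both arms are compared under the same programme.
- *86% of iron/folate pregnancies (54,000/63,000) have no concurrent comparison.* The split in step 3 fits exactly but is inferred. The summary speaks of standard-care villages that continue and of surveillance in non-intervention villages. Section VIII.B.1 lists 99 + 119 + 109 = 327 villages in the three districts against about 300 in the trial, plus the city of Mataram. Whether any of these are the designated villages is not stated.
- *Women in the trial take a known multiple of the usual total dose.* The government course is a minimum, compliance is unknown, and the summary says monthly packs of 30 are already MOH practice. Only the per-tablet ratios are firm; the course difference rests on section IV alone.
- *The programme effect will be overstated.* Nothing in the protocol fixes the direction.

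**Conclusion.** The point holds and should be fixed. The Outcomes paragraph names the wrong comparator: per tablet the control has 0.5 times the iron and 1.6 times the folate of the current tablet. The contrast of the iron/folate arm with non-intervention areas or baseline mixes promotion, midwife attendance, tablet change and calendar time, and is not stated to be randomised. It cannot support a separate effect of education and social marketing, of midwife attendance, or of individual components.

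The per-tablet figures and the use of the government tablet in pre-intervention areas are explicit. That the powered contrast is mostly before versus after (67% of comparison pregnancies from the baseline) assumes starts at months 0, 3 and 6; this reproduces both 54,000 and 126,000, but other concurrent villages may exist. The bias has unknown size and sign. The randomised estimate of multi-micronutrients against the 30 mg/400 µg tablet is not affected.

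**What to change.** - **Executive Summary, Outcomes:** name the comparator as the 30 mg iron/400 µg folate tablet.
- **Executive Summary, Outcomes and Sample Size, and section VIII.B.12:** describe the contrast as the non-randomised difference associated with the whole programme package, including the changed iron/folate tablet and its schedule, and subject to calendar-time differences.
- **Section VIII.B.8:** drop the claim to quantify the effect of midwife attendance.
- **Sections V and VIII.B.12:** limit component and cost-benefit claims to two parts, the programme package (with the changed iron/folate tablet) and the added micronutrients.
- **Section VIII.B.3:** at most a note that the package includes the tablet change and that the contrast is not randomised.

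No arm, sample size or data collection changes. The cost is a narrower programme conclusion: a package difference in place of an effect of education, social marketing or midwife attendance.

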## 2. *Design and Methods*

The proposed SUMMIT activity is a double blind, community-based, cluster-randomized, controlled intervention designed to assess the relative impact of multi-micronutrient supplements compared to iron/folate supplements on maternal mortality, infant mortality and low birth weight. Pregnant women will be randomized to one of approximately 300 clusters defined by the geographic area serviced by a trained midwife. This means that all women attended by a particular midwife will receive the same type of supplement. Clustered randomization was chosen due to the logistical and scientific difficulties associated with individual randomization in large scale longitudinal trials. Pregnant woman will be provided with either a daily multi-micronutrient supplement containing iron, folate, vitamin A, and zinc, along with additional B vitamins, minerals, anti-oxidants (for precise composition, see Appendix 3a), or an identical-looking daily supplement containing 30 mg iron and 400 µg folate. There will be no blank placebo group because iron/folate supplementation distribution to pregnant women is the current policy of the GOI.

The intervention will be preceded by a 6-month baseline demographic surveillance period to estimate area-specific maternal and infant mortality rates. Supplementation will then be phased in step-wise by implementation in 1/3 of the villages over 3 successive 3-month intervals. Women who refuse to be included in the trial and those in the pre-intervention areas will receive the standard GOI iron/folate tablets. The GOI iron/folate tablets will, therefore, not be withdrawn from the island but will only be used for individuals not enrolled in the intervention portion of the activity.

Supplements will be provided free to all women with a confirmed pregnancy, from the first antenatal consultation up to three months postpartum. As a joint activity between HKI and the GOI, the existing government system will distribute the supplements to pregnant women and the government-trained midwives will be involved in monitoring the health impact. HKI project staff will also encourage the midwives to provide maximum supplementation coverage. Additional non-invasive surveillance will be carried out by HKI project staff to allow adequate assessment of compliance and health impact.

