## 3. *Sample Size*

The sample size is influenced by the minimal desirable detectable effect of the intervention, the event rate of the outcome, and the duration of the intervention. The desired detectable effect is influenced by the magnitude of the plausible effect size and the importance of the preventable event. Initial estimates of a plausible effect size of multi-micronutrient supplementation on maternal mortality can be guided by childhood

mortality-related effects observed for other micronutrients such as vitamin A and iodine, which range from 20-70%. While acknowledging that physiological differences between children and pregnant women limit the utility of such information, additional perspective is gained from the results of the NNIPS-2 study which described a vitamin A-mediated 40% reduction in mortality related to pregnancy. Given the relatively low-cost of a prenatal nutrient-based intervention, the documentation of a 20-30% effect, especially under programmatic settings, would be important. The estimates of the maternal mortality ratio in various districts on Lombok range from 400 to 800 maternal deaths per 100,000 live births. For this intervention the unit of randomization will not be the individual woman, but the area or cluster of communities administered by the midwife. This improves logistical feasibility but reduces statistical power due to the potentially correlated outcomes within each cluster. Given the estimated between-cluster variability in MMR, we have calculated that a 20% increase in sample size is needed to compensate for the loss of statistical power from the cluster-based randomization. We further anticipate a loss to follow-up of approximately 10%. Lastly, because not all pregnancies result in a live birth, it is estimated that the required sample size be increased an additional 15% to compensate for abortions, miscarriage, and stillbirths. Given these factors, the sample size table below presents the number of pregnancies required to obtain significance for various observed reductions in MMR for the proposed 2-arm design.

| Detectable
reduction
(%) | Total pregnancies needed by baseline MMR
(deaths/100,000 live births) |                |                |
|-----------------------------------------|----------------------------------------------------------------------------------|----------------|----------------|

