## *6. Randomization to treatment*

As described above, the unit for randomization to treatment will be the geographic area serviced by or assigned to the trained village midwife. All pregnant women living in the village of a particular midwife will receive the same supplement. Each of the 300 midwives in the distribution areas will receive a supply of one of the two supplements. Randomization of supplements to 300 midwives will be carried out by a computer

generated randomization protocol optimized to limit the occurrence of identical codes assigned to adjacent midwives. The prognostic heterogeneity and design effect of the randomization will be assessed at baseline using data collected from the demographic surveillance.

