## *12. Data management and analysis*

The first check of the forms will be performed in the field by the field supervisors. Data entry will be done using the *SPSS for Windows* program. Data will be entered in batches, and 10% of each batch will be cross-checked by data-entry supervisors. Batches for which unacceptable error rates are obtained will be re-entered and checked until acceptable

quality standards are met. The data-entry program will prohibit entry of invalid or impossible values and generate a query for follow-up. After data have been entered, additional outliers will be identified and checked against the original questionnaires. Queries regarding unclear or incomplete data will be referred to the field for appropriate follow-up. This system has been field-tested by the HKI NSS and functions well. Primary analyses will compare key outcome event rates event rates, MMR, MMRT, PNMR, and LBW in the multi-micronutrient group with the iron/folate group. However, the SUMMIT activity will not only provide information concerning the impact of micronutrients on these indicators, but it will also assess the specific impact of activities accompanying the intervention such as promotion of prenatal care and social marketing. This will be done by comparison of event rates in the pre and post-intervention areas for the iron/folate arm. This enables one to individually assess the impact of the various components of the SUMMIT activity on the key health outcomes. Relative cost-benefit analyses can therefore be carried out for the various interventions.

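### Village mortality recorded before launch has no stated role in the comparison of the two supplements; adjusting neonatal and infant mortality for it would be an optional, nearly free improvement, not the correction of an error

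*Protocol*

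**What the plan says.** - Executive Summary, Sample Size: "Data concerning outcome variables in the absence of the intervention will be collected during the phase-in period prior to enrollment". The purpose given there is the contrast between the iron/folate arm and non-intervention areas.
- Section VIII.B.4 (Demographic Baseline Survey): surveillance begins six months before distribution, covers about 10,000 births in each of three zones, and is to estimate maternal and infant mortality. It starts with women, and their children are added afterwards. Precision for infant mortality is stated by zone.
- Section VIII.B.6 (Randomization to treatment): "The prognostic heterogeneity and design effect of the randomization will be assessed at baseline using data collected from the demographic surveillance". The allocation is constrained only to limit neighbouring midwives receiving the same code.
- Section VIII.B.3 (Sample Size): "a 20% increase in sample size is needed to compensate for the loss of statistical power from the cluster-based randomization". The 20% is derived from variability in MMR. The section claims that at least a 10% change in neonatal and post-neonatal mortality can be detected.
- Section VIII.B.12 (Data management and analysis): "Primary analyses will compare key outcome event rates event rates, MMR, MMRT, PNMR, and LBW in the multi-micronutrient group with the iron/folate group". No model, test or covariate is named.

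**The concern.** Village-to-village differences in underlying mortality are the part of the error that more women in the same 300 villages cannot remove. The protocol meets them with a larger sample. It also plans to hold, for the same villages, a pre-supplementation measure that should predict later mortality. Because that measure predates supplementation, adjusting for it cannot bias the comparison of the two supplements. If village rates differ and persist, the adjustment narrows the interval for infant mortality including neonatal mortality, a main outcome, without enrolling anyone else. The document assigns the data to other purposes and does not mention this one.

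**Working it through.** **Inputs**
- Clusters: "one of approximately 300 clusters defined by the geographic area serviced by a trained midwife" (section VIII.B.2); 150 per arm assumed.
- Trial live births per village: 126,000 / 300 = 420 pregnancies; 420 × 0.85 = 357.
- Baseline births per village: 3 × 10,000 / 300 = 100.
- Neonatal mortality p = 0.046; target 10% relative reduction, to 0.0414 (section VIII.B.3).
- Design criteria: "with a power of 80% and significance level of 0.05" (Executive Summary); two-sided reproduces the tables.
- Between-village coefficient of variation k for neonatal mortality: not given, so a range is shown.

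**The plan's own figure.** For 0.046 against 0.0414, the two-proportion formula with continuity correction gives about 31,435 live births per arm. Then 2 × 31,435 × 1.20 × 1.10 = 82,988, against 83,012 in the table. So the neonatal figure carries the 1.20 inflation that the text derives for MMR.

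**What 1.20 implies.** Design effect = 1 + (357 − 1) × k² × p/(1 − p). Setting this to 1.20:
- neonatal mortality, p = 0.046: k = √[(0.20/356) × 0.954/0.046] = 0.108
- MMR 400, p = 0.004: k = √[(0.20/356) × 0.996/0.004] = 0.37

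**Gain from adjustment**, at village level:
- V = (kp)² + p(1 − p)/357
- Reliability of the baseline rate R = (kp)² / [(kp)² + p(1 − p)/100]
- Adjusted V = V − (kp)² × R × r², where r is the correlation of true village rates over time
- Power = Φ[0.1p / √(2V/150) − 1.96]

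Worked for k = 0.25, r = 1:
- (kp)² = 0.00013225 and p(1 − p)/357 = 0.00012292, so V = 0.00025517.
- R = 0.00013225 / (0.00013225 + 0.00043884) = 0.232.
- Removed: 0.00013225 × 0.232 = 0.0000306, which is 12% of V.
- Power goes from Φ(2.494 − 1.96) = 70% to Φ(2.658 − 1.96) = 76%.

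| k | Design effect for neonatal mortality | Variance cut, r = 1 | Variance cut, r = 0.7 | Power, unadjusted to adjusted (r = 1) |
|---|---|---|---|---|
| 0.108 | 1.20 | 0.9% | 0.4% | 90.6% to 90.9% |
| 0.15 | 1.39 | 2.7% | 1.3% | 86.2% to 87.1% |
| 0.25 | 2.07 | 12% | 5.9% | 70% to 76% |
| 0.37 | 3.35 | 28% | 14% | 50% to 64% |

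At a design effect of 1.20, even perfect knowledge of each village's risk could remove no more than 0.2/1.2 = 16.7% of the variance. A baseline of 100 births holds about 4.6 neonatal deaths, and its reliability at k = 0.108 is only 0.05.

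**Sensitivity.** Using all 54,000 non-intervention pregnancies gives 54,000 × 0.85 / 300 = 153 births per village on average. The variance cuts become 1.3%, 4%, 16% and 35%. That count includes the phase-in, so pre-launch time differs between waves.

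**Maternal mortality.** 100 births × 0.004 to 0.008 = 0.4 to 0.8 maternal deaths per village in six months, too few to carry useful information.

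**The case against.** The strongest reply is that choosing covariates is ordinarily left to the statistical analysis plan, which is not at hand. Section VIII.B.12 is a short paragraph that fixes no model. Section VIII.B.8 already foresees midwife activity and community cooperation entering the analysis as effect modifiers, and section VIII.B.6 foresees examining prognostic heterogeneity. This stands: silence is not a decision against adjustment, and nothing here is contradicted or wrongly stated.

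The second reply concerns size, and it also stands. At the design effect the plan itself uses for neonatal mortality, the gain is about 1% of variance and 0.3 power points. Larger gains need more variation than 1.20 implies. The 28% case carries a maternal-mortality coefficient of variation over to neonatal mortality, which no section supports. Stable rates are also doubtful: social marketing, midwife training and promotion of attended delivery come between baseline and trial, and women migrate to their parents' homes to deliver.

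A reader might infer that the surveillance data serve only the programme contrast and the heterogeneity assessment. That goes too far: sections V, VIII.B.2 and VIII.B.4 also name area-specific rates, migration, household composition, logistics and linkage to the nutrition surveillance database. None of these, however, is a use in the comparison of the supplements. A reader might also infer that usable village-level infant deaths are already assured. The text is looser: children are added after the women, and precision is claimed by zone.

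**Conclusion.** The point holds as an optional improvement. The protocol plans to collect pre-supplementation births and infant deaths, gives village baseline mortality no role in comparing the two supplements, and does not exclude one. The expected gain for neonatal mortality runs from about 1% of variance at the protocol's own design effect to 12% at k = 0.25. It reaches 28% only if the design effect is about 3.4. These figures assume 357 trial and 100 baseline births per village and stable village rates; about half remains at a correlation of 0.7.

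It would be tempting to conclude that the trial gives up substantial precision, or that it has only 50% to 70% power for a 10% reduction in neonatal mortality. The documents do not support either, because they give no between-village variation for that outcome. The case for the change rests on its low cost and freedom from bias, not on a demonstrated loss.

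**What to change.** - In section VIII.B.12, state that the comparison of neonatal and infant mortality between the two supplement arms adjusts for each village's pre-launch neonatal (early infant) mortality rate from the demographic surveillance, and that unadjusted rates are reported alongside.
- Use the same pre-supplementation window in all villages, since the phase-in gives later waves a longer pre-launch period. An early infant rate suits this better than 12-month mortality, which cannot be complete for births in so short a window.
- In section VIII.B.4, make sure that early infant deaths are recorded by village before launch. A later analysis plan could not recover them.
- Leave MMR and MMRT without a village maternal baseline.

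The cost is one sentence and one covariate in the analysis, plus confirmation that the planned surveillance captures these deaths by village. No further women are needed.
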